## PRE-RCT WORKSHOPS (pre-work AIM 1)

**12.1.i Pre-trial formative workshop** We will conduct a workshop among key stakeholders including providers, health care leaders from central and county MOH as well as WLWH receiving HIV care. We will purposefully recruit health care leaders from central and county MOH who represent both HIV and reproductive health decision makers (including those involved with care integration). We anticipate that each county will have 1-2 county district health officers (n=2-4). In addition, we will recruit family planning providers and clinic leadership from representative clinics (5 from Western and 5 from Nairobi). We will purposefully recruit WLWH with a range of RH experiences (FP continuer, FP initiator, FP switcher, FP discontinuer, intended pregnancy, and pregnancy ambivalence) This workshop will inform SMS development, different user ‘tracks’ which depend on women’s reproductive life plans. This type of qualitative data on HIV/SRH topics have previously been shown to be acceptable in our prior studies, including among WLWH.([48](#_ENREF_48), [68](#_ENREF_68), [69](#_ENREF_69), [76](#_ENREF_76)).

| **Population** | **Providers** | **WLWH** | **Policymakers** |
| --- | --- | --- | --- |
| **Role** | Future end users | Empower Beneficiaries | Shape MW Empower implementation context |
| **Eligibility criteria** | - Age ≥18 - Provider (HIV or FP) at clinic | - HIV-infected - Reproductive age (18-45; 14-17 if emancipated minors) | - Age ≥18 - Member of national or county health department/ reproductive health division |
| **Objectives** | - Optimize counseling strategies - Refine SMS messaging - Define counseling and SMS flow - Refine SMS response & referral protocol/decision guide | | - Define Empower context in policy agenda |

Pre-trial data from the workshop will be directly integrated to support intervention modifications, including optimizing tablet-based counseling strategies, SMS content and flow of the intervention. We will conduct the workshop within the IMB (Information Motivation Behavioral) based conceptual framework (Figure 3) which will help maximize intervention acceptability, feasibility and durability.

## **AIM 2 – In-depth Interviews and Focus Group Discussions (FGDs)** (Acceptability, appropriateness, feasibility, and scalability of Mobile WACh Empower implementation under real-world conditions)

**12.1.ii IDIs and FGDs during the trial (Aim 2)** FGDs will be conducted with WLWH during the trial to get their feedback on the counseling tool. Two FGDs will be conducted, stratified by age, at each intervention site (10 WLWH FGDs in total) – one with young women (<25 year olds) and second with older women (>=25 years old). All FGDs will include 6-10 women per FGD and they will be recruited after enrollment. During the trial, we will also conduct IDIs with healthcare providers to understand how they are using the counseling tool to provide reproductive health counseling to WLWH and gather their inputs to improve the counseling tool. We will also we will ask them to fill a short survey on acceptability (i.e. your perception if the Empower counselling tool is agreeable, palatable, or satisfactory), appropriateness (i.e. perceived fit, relevance, or compatibility of the Empower counselling tool in your current role as a healthcare provider), and feasibility (i.e. the extent to which the Empower counselling tool can be successfully used or carried out within a healthcare facility) of the counseling tool. This information would help in revising the counseling tool and improve its implementation. From each intervention site, we will interview ~3 providers who are currently employed at the intervention facility, provide FP services to WLWH, and who’ve interacted with the counseling tool (~15 IDIs in total).

**Exit FGDs (Aim 2)** FGD recruitment will begin when 50% of women exit the trial. We will conduct 2 FGDs among WLWH exiting the trial at 24 months at intervention sites (10 WLWH FGDs total). FGDs will be stratified by RH outcome (FP continuer, FP switcher, non-pregnant FP discontinuer, pregnant FP discontinuer, pregnancy ambivalence); each site will be randomly assigned to recruit women for 2 of these groups (**Figure 10**). We will purposely recruit women with a range of SMS engagement based on percentiles of SMS responses (≤25, >25-75, and >75%ile) to capture varied user experiences within FGDs. We will also conduct FGDs with HIV providers (1 per intervention site). All FGDs will include 6-10 people per FGD. FGDs will allow participants to describe experiences or situations/issues related to RH needs, in their own words and in a way they would
[figure not shown]
commonly discuss these concepts. FGD sample sizes are intended to capture diversity in experiences, while also reaching thematic saturation; i.e., when no new concepts emerge with subsequent FGDs. However, we will increase the number of FGDs with WLWH if new themes emerge at the end of FGDs. Provider sample size is limited to the number of providers at each intervention site.

| **Table 5. Concepts assessed during FGDs at study end (24 months) (Aim 2)** | |
| --- | --- |
| ***WLWH*** *- Analysis guided by IMB Theory* | ***Providers***  *- Analysis guided by CFIR* |
| Identify community norms on intervention barriers & facilitators   - Perspectives on utility of SMS - How intervention influenced information & motivation informing RH decision-making - Impact on RH behaviors - Intervention preferences, strengths, limitations | - Key influences on intervention implementation - Evaluate context, climate, resources, and intervention components that impact intervention acceptability, feasibility, and appropriateness - Identify strategies for future intervention scalability |

FGD topic guides for WLWH will be grounded in IMB Theory and will evaluate how Mobile WACh Empower influenced information and motivations informing RH decision-making, as well as intervention impact on RH behaviors, including self-efficacy for safe pregnancy/FP use and continuation **(Table 5)**. Guides will assess acceptability through participant preferences, strengths, and limitations of the intervention. Provider FGD guides will be grounded in the LMIC adapted Consolidated Framework for Implementation Research (CFIR).([90](#_ENREF_90), [91](#_ENREF_91)) CFIR is a flexible, meta-theoretical framework designed to describe heterogeneity in implementation across settings, and the relative effect of key constructs in influencing implementation outcomes.([90](#_ENREF_90)) Provider FGD guides will elicit information on individual and health systems influences on acceptability, feasibility and future scalability, and key information about the role of context in influencing implementation.

A Kenyan team trained in qualitative research methods will conduct all IDIs (~1 hour/IDI) and FGDs (~1.5-2 hours/FGD) in English, Kiswahili, or Dhuluo, depending on participant preferences. IDIs and FGDs will be audio recorded, transcribed, and translated into English if necessary. Following IDIs and FGDs, the researcher that led the discussion will complete a targeted debrief report to share overall IDI/FGD impressions and preliminary content discussed with investigators in real time.([92](#_ENREF_92))

**12.1.iii IDI and FGD analysis procedures**

We will analyze transcripts using directed content analysis([93](#_ENREF_93)) and ATLAS.ti. [name] will lead the research team to develop a preliminary codebook based on specific IMB theory or CFIR constructs, and additional themes identified in debriefing reports. The codebook will be reviewed against full length transcripts and iteratively revised until all key themes are captured in the coding structure. After completing a consensus coding process and ensuring consistent application and interpretation of codes, all transcripts will be coded by 2 team members. Based on IMB theory (WLWH transcripts) or CFIR (provider transcripts), code co-occurrence tables and queries will be used to identify key influences on user acceptability, appropriateness, feasibility and future scalability of Mobile WACh Empower. Thematic network analysis will be used to group identified influences into larger thematic categories and describe the network of related concepts influencing user experiences and health systems considerations, and possible strategies to overcome or harness identified barriers and facilitators. **Findings from the IDIs, FGDs and surveys to assess RH outcomes will be integrated into future designs to 1) better understand causality and mechanisms of action for specific outcomes and 2) adapt the intervention and Mobile WACh Empower platform for scale, including refinement of SMS messages for this environment, population, and specific outcomes, as well as integration within existing workflows.**

## Aim 3- Health economic analysis and mathematical model

Micro-costing and time-motion observation studies will be conducted to estimate the incremental cost of implementing Mobile WACh Empower from a health system’s perspective. We will collect trial costs from facilities utilizing standardized cost menus. Costs will be divided into categories (start-up, training, clinic space, human resources, supplies and equipment). Resource use will be assessed by examining study budgets, expense reports, and conducting study staff interviews. Capital and start-up costs will be annualized assuming a useful life of 5 years and discounting at 3% following standard guidelines.([94](#_ENREF_94)) We will conduct time-motion observation of intervention activities for up to 50 patient/provider interactions to measure provider time needed for counseling in intervention and control facilities, and staff time to operate and respond to Mobile WACh SMS. Research time (e.g., informed consent) and supplies will be excluded. Costs of labor and FP commodities will be measured in the trial. We will use the contraceptive method mix observed in Mobile WACh Empower, and micro-costing data, to estimate average cost per FP user, updating a historical model on costs of FP on PMTCT.([95](#_ENREF_95))

**MTCT Model** We will adapt an existing MTCT Markov model (*Meisner/Drake review Int AIDS Soc 2021*)([64](#_ENREF_64)), including upstream elements related to pregnancy risk and intentions, and economic impact of Mobile WACh Empower (including intervention costs incurred/averted). Current model parameters include time since HIV diagnosis, ART use/adherence, infant ARV use, viral suppression, and breastfeeding. We will estimate costs of ART provision and other healthcare expenses from the literature. We will adapt our model to incorporate estimates of unintended pregnancies following prior methods*(*[*95*](#_ENREF_95)*)*, including: unmet need for FP among WLWH (from Mobile WACh Empower trial), current maternal ART and infant ARV regimens, and contraceptive failure rates from developing countries. ([96](#_ENREF_96)) Reduction in births among WLWH who desire pregnancy prevention (need for FP) will be calculated based on the ratio of the contraceptive index (1-1.08x contraceptive prevalence rate [CPR] x efficacy) for women who receive the intervention vs SOC (current CPR and unmet need).([95](#_ENREF_95)) We will calibrate the model to estimates of unintended pregnancy reported by Track 20 and MTCT rates in Kenya. We will project intervention impact on unintended pregnancies and MTCT, calculating incremental cost-effectiveness ratios (ICERs) as the ratio of costs divided by the difference in health outcomes (unintended pregnancy and infant HIV) of the intervention compared to the SOC over a 20 year time horizon. Consistent with guidelines, we will discount costs and health benefits at 3% annually; ICERs below Kenya’s per capita gross domestic product will be considered cost-effective([97](#_ENREF_97)). We will conduct sensitivity analyses to identify influential assumptions.

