**Aim 3:** To estimate the cost and cost-effectiveness of implementing Mobile WACh Empower in HIV clinics in Kenya on unintended pregnancies and MTCT. Approach: We will conduct micro-costing and time-motion observations to estimate intervention costs from a health system perspective. We will combine costs and trial outcome data from Aim 1 in a mathematical model to project the health and economic impact of implementing Mobile WACh Empower in Kenya, including costs per unintended pregnancy and MTCT averted.

*Hypothesis:* *Mobile WACh Empower will be a cost-effective approach for preventing unintended pregnancies.*

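### Aim 3 applies a single per-capita GDP threshold to cost per unintended pregnancy averted and cost per infant HIV infection averted, with no common health unit and no support for valuing either event at one GDP per head

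*Protocol*

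**What the plan says.** The MTCT Model paragraph under Aim 3 (Health economic analysis and mathematical model) defines the ICERs with the denominator "divided by the difference in health outcomes (unintended pregnancy and infant HIV) of the intervention compared to the SOC". The projection runs "over a 20 year time horizon", and "we will discount costs and health benefits at 3% annually". The decision rule follows: ICERs below Kenya's "per capita gross domestic product will be considered cost-effective". The paragraph does not say which ICER the rule governs. It closes with a general commitment: "We will conduct sensitivity analyses to identify influential assumptions".

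Section 11.2 confirms the units. Aim 3 is to project impact "including costs per unintended pregnancy and MTCT averted". Its hypothesis is that the intervention "will be a cost-effective approach for preventing unintended pregnancies"; infant HIV is not named there.

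The protocol contains no DALY, QALY, life-year or other common health unit. It gives no monetary value for the threshold, no separate threshold for each outcome, and no rule for the case where the two ICERs fall on opposite sides of it.

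**The concern.** A single money threshold is a coherent rule across outcomes only if one unit of the denominator represents the same amount of health each time. One unintended pregnancy averted and one infant HIV infection averted do not. Setting both ICERs against the same amount treats the two events as equally valuable and fixes that value at one year's GDP per head. The protocol supports neither step.

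Two consequences follow. The same model run can be labelled cost-effective on one ICER and not on the other, and the favourable label can be brought forward once results are known. Also, a verdict read from one ICER alone depends on an arbitrary price for that event.

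This matters because Section 16 (Study Limitations) says the trial lacks power for unintended pregnancy and MTCT and relies on the model for them, and Section 8 presents the cost-effectiveness work as information for budget decisions in Kenya.

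**Working it through.** The protocol gives no ICER and no GDP figure, so there is no stated number to reproduce. The check is algebraic.

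**Inputs**
- T: the threshold, one Kenyan GDP per head, normalised to 1 (rule from the MTCT Model paragraph).
- ΔC: incremental cost, intervention versus standard of care. The same ΔC enters both ICERs.
- ΔP, ΔI: discounted unintended pregnancies and infant infections averted.
- m = ΔI / ΔP. This is not in the protocol. I assume 0.01 to 0.25.

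**Formulas**
- ICER per pregnancy = ΔC / ΔP
- ICER per infection = ΔC / ΔI = (ΔC / ΔP) / m
- The verdicts conflict when ICER per pregnancy is below T but ICER per infection is not, that is, when m × T ≤ ICER per pregnancy < T (for m < 1 and ΔC > 0).

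**Results**

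| m (assumed) | Ratio of ICERs, 1/m | Cost per pregnancy giving conflicting verdicts | Cost per infection if cost per pregnancy = 0.5T |
|---|---|---|---|
| 0.01 | 100 | 0.01T to 1T | 50T |
| 0.02 | 50 | 0.02T to 1T | 25T |
| 0.05 | 20 | 0.05T to 1T | 10T |
| 0.10 | 10 | 0.10T to 1T | 5T |
| 0.15 | 6.7 | 0.15T to 1T | 3.3T |
| 0.25 | 4 | 0.25T to 1T | 2T |

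At 0.5T per pregnancy the verdicts conflict for every m in the table. At 0.2T they conflict for m up to 0.15 (0.2 / 0.15 = 1.3T) but agree at m = 0.25 (0.2 / 0.25 = 0.8T). At or above T both ICERs fail, and below m × T both pass.

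**What the algebra does and does not assume.** The relation between the ICERs is an identity once m is defined as ΔI / ΔP. The range for m is the assumption. The model includes viral suppression and ART adherence, and Table 4 lists viral suppression at conception as a modelled outcome, so infections may also be averted in pregnancies that go ahead. That raises m and narrows the band, which closes only when m reaches 1. If ΔC is negative and both outcomes improve, the intervention is cost-saving and no conflict arises.

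**The case against.** The strongest objection is that the hypothesis already fixes the unit. It concerns preventing unintended pregnancies, so the pregnancy ICER set against the threshold gives one verdict, and an infant-HIV ICER above the threshold would not contradict it. This stands. A reader might infer that the rule cannot settle the Aim 3 hypothesis; the text does not support that. What remains is that the single verdict depends on an unsupported price per pregnancy, and that the rule itself is not limited to that ICER.

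A reader might also infer from "as the ratio of costs divided by the difference in health outcomes (unintended pregnancy and infant HIV" that total rather than incremental costs form the numerator. The documents do not support that either. The measure is named an incremental ratio against standard of care, the model counts costs incurred and averted, and the micro-costing is said to estimate incremental cost. This is loose wording and not part of the point.

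It can further be said that the protocol cites a source for the threshold, which I have not seen, and that two outcomes may legitimately give two answers. Both are fair. But the protocol's own text attaches the rule to event-based ICERs and offers no argument for that use. The planned sensitivity analyses vary assumptions; no alternative threshold or health unit is named.

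Finally, the size of the disagreement rests on an assumed m. That is correct, and for this reason it is given as a range.

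**Conclusion.** The point holds in this form: the protocol states a rule, rather than leaving a detail open, and the rule sets one GDP-per-head threshold against ICERs in two unequal event units with no common health measure. For m between 0.01 and 0.25 (assumed), the ICERs differ 4- to 100-fold, and opposite verdicts arise whenever cost per pregnancy lies between m × GDP and 1 × GDP. A larger m shrinks that band, and a cost-saving result removes the conflict. Whether it would occur cannot be known from the protocol, which gives neither m nor any expected cost.

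The consequence is confined to the Aim 3 conclusion. It does not touch the design, sample size or analysis of Aim 1. It should be corrected before model results are available, because the choice of which ICER to headline is otherwise open.

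**What to change.** Choose one of two changes.

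1. Report cost per unintended pregnancy averted and cost per infant infection averted without a GDP verdict, and reword the Aim 3 hypothesis so that it no longer promises one. This is a text edit. The cost is giving up a yes/no conclusion.
2. If a verdict is wanted, apply the threshold only to incremental cost per DALY averted, and report the two event-based ICERs descriptively beside it. Count the lifetime health loss of infants infected within the 20-year horizon, since stopping the count at 20 years would cut off part of that loss, most of all for infants infected late. State how unintended pregnancy itself is valued. The cost is additional and contestable modelling assumptions, including disability weights and survival.

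Neither option needs further trial data.

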## 12.7 Study Materials

Equipment: The grant award includes support for SMS platform messaging delivery and receipt, 6 tablets, field office supplies (stationary, paper, toner), 6 laptop computers.

Personnel: The grant award includes support for KNH, UW and MOH investigators, clinic personnel, the data team, and two study coordinators (clinical coordinator (Nairobi based) and overall coordination (Seattle based)). Study personnel working in Kenya will be hired through KNH according to standard procedures.

## 12.8 Training Procedures

[name], [name], [name] will supervise training of clinical personnel in study procedures. This will include research ethics, neonatal health and FP counseling and completion of surveys.

##

## 12.9 Quality Assurance Procedures

Clinical care: No clinical care will be provided by study staff. However, SMS and referral procedures will be developed in accordance with Government of Kenya guidelines for the care of WLWH and reproductive health and family planning.  Data collected as part of the study will be abstracted from clinic medical records.

Adherence to protocol: Weekly reporting of enrolment, follow-up, medical complications and results will enable us to monitor that the study is running according to approved protocols.  Frequent reporting will also enable us to quickly respond to any problems that arise during the study.

# 13. ETHICAL CONSIDERATIONS

## 13.1 Consent explanation

Please see the attached consent forms:

Consent 1: RCT study participation

Consent 2: Pre-RCT Workshop discussion

Consent 3: Post-RCT FGD women

Consent 4: FGD with women

Consent 5: IDI with provider

## 13.2 Institutional Review Board

This is a collaborative research proposal that will involve field procedures in Nairobi and data analyses in Nairobi and Seattle. The study will be reviewed by the Kenyatta National Hospital/University of Nairobi (KNH/UON) Ethics and Research Committee (ERC), and the University of Washington Institutional Review Board (IRB). The study will not recruit subjects prior to approval from both the UW IRB and the KNH/UON ERC.

## 13.3 Risks to subjects

**Physical:** The study involves no medical interventions therefore we anticipate no risk of serious harm to participants.

**Other:** SMS: There is a potential risk of disclosure of an individual’s person information to others in situations where phones are shared or stolen. We will minimize these risks through counseling in the informed consent process and ensuring women understand the type of messaging that will occur.

Access to clinical records: There could be a breach of confidentiality in the process of retrieving participants’ medical records. This will be mitigated by training all study staff on data management and storage to ensure confidentiality of sensitive data is maintained.

Loss of Confidentiality in Workshop and FGD: Women will be notified that by participating in the Workshop and FGD, loss of confidentiality is a possible risk of participating. They will be informed that this is very unlikely as every measure will be taken to ensure confidentiality.

Alternative treatments or procedures: Not applicable

## 13.4 Protection against risks

Informed consent: Study staff will give potential participants verbal and written information about the study. Study staff will go through the consent form and will explain to each potential participant the purpose, risks and benefits of the study in the language of the participant’s choosing. Participants will be informed that they can choose to withdraw from the study at any point and for any reason. They will also be informed that participation is completely voluntary. Participants will have a chance to ask questions about the study and offered participation. Oral consent will be obtained at time of enrollment. We will obtain electronic written informed consent for study participation into the RCT. Study staff will go through the consent form and will explain to each potential participant the purpose, risks and benefits of the study in the language of the participant’s choosing. Participants will be informed that they can choose to withdraw from the study at any point and for any reason. They will also be informed that participation is completely voluntary. Participants will be offered a copy of the consent form to keep. Participants who agree to participate in study activities will sign the informed consent form electronically in the presence of the study nurse using REDCap’s signature field in which a participant will use a finger or stylus to mark their signature on the study tablet. The electronic signatures will be saved on a secure REDCap server (managed by the University of Washington Institute of Translational Health Sciences), separate from study data. The electronic signature is not a digital signature. Electronic collection of consent signatures allows for real time consent quality monitoring, as well as secure, encrypted, storage of participant names and signatures. Before signing, the study staff will explain to participants that signing the form electronically will serve as the equivalent of signing a physical document. Study staff will help participants navigate the electronic signature and consent process. Once a participant electronically signs, the study staff will ask the participant to review the inputted information to certify that it is correct, before submitting to the server. Study staff will have access to the technology required for electronic consenting. Consenting will be conducted face-to-face if possible, according to Kenyan COVID-19 precaution guidelines, but may be conducted over the phone to adhere to social distancing from KNH and UW ethical research guidelines. Study staff will have a dedicated phone available for client use if clients do not have a personal phone that can be used. These phones will not hold any participant information and will be sanitized between uses. If a participant cannot read or has trouble reading, study staff will read the form to participants. Study staff will also review the form with all participants after they have finished reading it to ensure participant understanding. Participants who cannot read or write will be able to provide documentation of writing consent by making a mark, such as an ‘X’ on the subject signature line after hearing the consent form read to them in the presence of a witness who signs and dates the consent form. The witness will be impartial (not a member of the research team).

SMS: There is a potential risk of disclosure of an individual’s person information to others in situations where phones are shared or stolen. However, we will not send any sensitive information via text. Study staff will specifically demonstrate example messages, to ensure potential cohort study participants agree to receipt of this information. Participants will only be enrolled once they understand study procedures and find the messaging acceptable.

Access to clinical records: There could be a breach of confidentiality in the process of retrieving participants’ medical records. This will be mitigated by training all study staff on data management and storage to ensure confidentiality of sensitive data is maintained. Databases will not include patient identifiers and will be encrypted and password protected.

Loss of confidentiality in workshops and FGDs: In order to protect participant confidentiality, participants will be identified in audio recordings and transcripts only by their study ID, not their name. Workshop and FGD participants will be counselled on the importance of not sharing the identity of other participants or details regarding the content of the discussion with anyone outside the group.

DSMB: We will establish a DSMB who will regularly monitor protocol implementation, adverse events and study outcomes.

Undiagnosed conditions: It is possible we will detect previously undiagnosed conditions such as depression and intimate partner violence. Participants will be referred for appropriate health and social services.

SMS withdrawal: Participants in the intervention group may withdraw from receiving SMS messages at any time. Study staff will complete an SMS Withdrawal form for any participants who wish to withdraw from the system. Participants who withdraw from SMS can continue or withdraw from the study.

Study withdrawal: Participants may withdraw from the study at any time for any reason. Study staff will complete a Study Termination form for any participants choosing to terminate early. All data collection and SMS messaging will discontinue at that point.

